## Abstract

**Background:**

As a lifetime disorder, ulcerative colitis (UC) is an inflammatory bowel disease (IBD) that affects quality of life and also demands long-term interventions. In spite of considerable side effects and sometimes restricted uses, efficient medications are available for UC treatment. Some in vitro and in vivo examinations have correspondingly introduced ginger and its active components with antioxidant, anti-inflammatory, and anti-ulcerative properties. Therefore, this trial aims to evaluate the effect of ginger supplementation on patients with active UC.

**Methods:**

This study will be a 12-week, double-blind, parallel-group, randomized, controlled trial (RCT) in which 44 patients will be allocated to ginger and placebo groups receiving basic routine treatments plus ginger or placebo capsules, respectively. The primary outcomes are inflammatory markers (TNF-α and hs-CRP) and total antioxidant capacity.

**Discussion:**

The findings of this trial will provide evidence on the effect of ginger on patients with active UC.

**Trial registration:**

Iranian Registry of Clinical Trials, IRCT20190129042552N1. Registered on 21 June 2019.

## Background

Inflammatory bowel diseases (IBDs) are known as chronic recurrent disorders of the gastrointestinal tract and comprise two major types—ulcerative colitis (UC) and Crohn’s disease (CD)—that can result in poor quality of life and require long-term medical and/or surgical interventions [1]. The prevalence rates of UC have been reported as 37.5-248.6 and 4.9-505 per 100,000 individuals in Northern America and Europe, respectively [2]. Similarly, a systemic review also reported the prevalence rate of UC in Iran of 35.52 per 100,000 in the general population [3]. This disorder mainly develops in the rectum, and in some cases, it extends to the proximal colon, sometimes affecting the entire colon [1]. Moreover, its symptoms include diarrhea, abdominal pain, and fever, as well as clinical signs of intestinal obstruction and bleeding, depending on the location of the disease [1].

This inflammatory condition involves a wide range of alterations in inflammatory mediators such as tumor necrosis factor-α (TNF-α), interleukin-6 (IL-6), high-sensitivity C reactive protein (hs-CRP), and also a decrease in antioxidant capacity [4]. Furthermore, variations in microRNA (miRNA) expression have been reported in UC. MiRNAs are a group of single-strand, noncoding, RNA molecules that are 22 nucleotides long on average and regulate post-transcription gene expression [5].

MiR-21 is particularly relevant to intestinal inflammation in which overexpression has been reported in both patients and experimental models with IBD. MiR-21 play an important role in IBD pathogenesis (via gene expression regulation) [6], intestinal barrier function [7], intestinal microbiome [5], and the activation and differentiation of T cells [8, 9].

Pharmaceutical drugs for UC treatment include aminosalicylates (e.g., sulfasalazine and mesalazine), immunosuppressants (e.g., glucocorticoid, azathioprine, methotrexate, and cyclosporine A), and biologics (e.g., infliximab and adalimumab). Despite the efficacy of such drugs, some considerable side effects can limit their long-term use [10]. Therefore, the development of efficient, safe, and new therapeutic and complementary agents is necessary. In this respect, ginger, as an important agents, has been considered for its effects on chronic inflammation [11].

Ginger, viz. *Zingiber officinale* from the Zingiberacea family, is a rhizome widely used as a spice [12], which contains many active phenolic components such as gingerol, shogaol, and zingeron.

These components show antioxidative, anti-inflammatory, and immunomodulatory properties. A clinical trial evaluated the effect of ginger supplementation in older patients with osteoarthritis. This trial show a reduction in inflammatory markers like TNF-α and IL-1β [13]. In addition, another trial reported a reduction in nitric oxide and hs-CRP levels in ginger-supplemented osteoarthritis patients compared to the control group [14]. A randomized clinical trial conducted by Aryaeian et al. showed that ginger supplementation could improve the disease activity score and modulate some inflammatory genes in rheumatoid arthritis patients [15].

Data also have revealed that ginger suppresses nuclear factor kappa B (NF_κ_B) and ameliorates UC in experimental models [16, 17]. In a study by Allah et al., ginger administration (400 mg/kg) significantly improved the effects of acetic acid-induced colitis by decreasing the weight-to-length ratio of the colon and macroscopic and microscopic manifestation of colon specimens. These effects were associated with a significant decrease in NFkB expression and a decrease in TNF-α, IL-10, and the total peroxide levels in the colon. In this study, the therapeutic effects of ginger were shown to be more than preventive effects [16]. Dileep et al. investigated the anti-inflammatory effects of an alcohol extract of ginger (700 mg/kg/day) in ulcerative colitis induced by acetic acid in rats. The results showed that increased levels of carbonyl protein, TNF-α, IL-1β, and prostaglandin E2 decreased significantly in the colon. Significant increases in the levels of superoxide dismutase, catalase, reduced glutathione, glutathione peroxidase, and IL-10 were also observed in this study. Histological examination revealed a decrease in bleeding and edema in the colon of the treated group [18].

To the best of the authors’ knowledge, no published data exist on the effect of ginger supplementation on patients with UC; therefore, a randomized controlled trial (RCT) will be designed to determine the effect of ginger supplementation on the clinical status, serum levels of some inflammatory markers (i.e., TNF-α and hs-CRP), total antioxidant capacity (TAC), and expression of miR-21 in patients with active UC.

### Hypothesis and aim

The research hypothesis addressed is that ginger supplementation along with taking standard medications improves clinical and biochemical parameters. The primary objectives of this RCT is to assay the effect of 12-week ginger supplementation on inflammatory markers (TNF-α and hs-CRP) and TAC in patients with active UC. The secondary objective will be also to determine clinical score and miR-21 expression. For all outcomes, including the primary and secondary outcomes, measurements will be made at the beginning and the end of the intervention, and changes from baseline within groups and final values between groups will be evaluated.

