### Sample size

The sample size was calculated according to primary outcomes (if data were available), and the maximum calculated sample size was considered. The sample size was based on the changes observed in the TNF-α in the study by Mozafari Khosravi [13] as a result of ginger supplementation. Considering a type I error of 0.05, a test power of 90%, and follow-up loss of 10%, the sample size required in each group was calculated to be 22 patients. To achieve the estimated sample size, all patients will be included in the study in case they meet the inclusion criteria and are willing to participate in the study.

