### Intervention

During the 12-week intervention, both groups will continue the use of the prescribed medications. Patients in the intervention group will receive three ginger capsules on a daily basis (i.e., one capsule after each main meal), and each capsule will also contain 1 g of dried ginger rhizome. Notably, a human equivalent dose had been calculated in an animal study [14] using a conversion factor [19]. Patients in the control group will receive three placebo capsules daily; each capsule will contain 1 g of starch as a placebo, which looks like a ginger capsule in appearance. Ginger and placebo capsules are being made by the Green Plants Life Company. The method and the time of taking the capsules are labeled on the bottles. Patients in both groups will be requested not to change their typical diet and physical activities and also avoid the use of nutritional or ginger supplements, ginger candy, and ginger seasoning, as well as ginger tea and other herbal remedies during the study.

Ginger and placebo capsules will be delivered in identical containers for 4 weeks. The patients will be asked to give back the containers at the end of each fourth week for use in calculating their compliance rate. To ensure the ordered use of capsules as well as accurate implementation of the RCT, researchers will contact the patients via phone calls or short message service (SMS) each week.

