### Measurements

At the onset of this RCT, demographic characteristics information will be collected via interviews and records, and relevant questionnaires will be completed. Weight will be also measured, while participants are wearing light clothes and no shoes, to 0.1-kg accuracy on a Seca scale, height will be measured, without shoes, using a 0.5-cm accuracy on a Seca stadiometer, and BMI will be calculated by dividing the weight (kg) by the height squared (m^2^).

In addition, the clinical status of the patients will be characterized by PMS and the Simple Clinical Colitis Activity Index (SCCAI) at pre- and post-intervention stages. Notably, the PMS is made up of three noninvasive parts of the complete Mayo score, which includes frequency of defecation, rectal bleeding, and a physician’s assessment of disease severity. Each of the parameters has a score from 0 to 3, and the maximum total score is 9. This score divides patients into those with inactive UC (i.e., in remission) and into those with active UC (i.e., mild, moderate, and severe). The clinical response is also defined as at least a 2-point reduction in the Mayo clinical score. The SCCAI includes the frequency of defecation during the night and day, defecation urgency, blood in stool, general sense of well-being, and external manifestations of the disease. The total score can range from 0 to 19.

Biochemical parameters consist of serum levels of TNF-α (ng/l), hs-CRP (mg/l), and TAC (u/ml) which will be evaluated by the enzyme-linked immunosorbent assay (ELISA) kits and miR-21 expression, which will be measured through reverse-transcription polymerase chain reaction (RT-PCR). At the beginning and the end of the study, a 5-ml venous blood sample (in a regular tube) will be collected in ethylenediaminetetraacetic acid (EDTA) tubes after approximately 12 h over-night fasting, and it will be centrifuged at 1500 g for 15 min and stored in −70 °C frigid temperature.

Physical activity will be evaluated by the short form of International Physical Activity Questionnaire (IPAQ) and calculated as MET-min/week. For dietary evaluation, 3 days of 24-h food recall (1 day of weekend and 2 days of the week) will be completed and then analyzed by Nutritionist IV software to determine the energy, protein, carbohydrate, and fat intake. Physical activity and dietary evaluation will be conducted at the onset and the end of the study.

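### The SCCAI is scored only at baseline and week 12 despite existing interim contacts, so early leavers give no post-baseline value, and final scores are compared without baseline adjustment

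*Protocol article*

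**What the plan says.** All references are to the protocol article.

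- **Schedule.** Hypothesis and aim sets two time points: "For all outcomes, including the primary and secondary outcomes, measurements will be made at the beginning and the end of the intervention". Measurements repeats this for the two clinical scales: "the clinical status of the patients will be characterized by PMS and the Simple Clinical Colitis Activity Index (SCCAI) at pre- and post-intervention stages".
- **Rank of the outcome.** "The secondary objective will be also to determine clinical score and miR-21 expression".
- **Comparison.** "changes from baseline within groups and final values between groups will be evaluated". Analysis adds a between-group comparison of percentage changes and a general linear model adjusted for confounders, with type of medication as the example. It does not name the baseline score as a covariate. Intention-to-treat is planned only where possible.
- **Existing contacts.** Under Intervention, "researchers will contact the patients via phone calls or short message service (SMS) each week", and "The patients will be asked to give back the containers at the end of each fourth week". The stated uses are correct capsule intake, proper conduct of the trial and the compliance rate. No symptom score is taken.
- **Expected loss.** Sample size assumes "a test power of 90%, and follow-up loss of 10" per cent.
- **Nature of the disease.** "Inflammatory bowel diseases (IBDs) are known as chronic recurrent disorders of the gastrointestinal tract".

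**The concern.** Clinical improvement is part of the research hypothesis, and the participants have moderate to severe active disease at entry. With one post-baseline time point and no early-withdrawal assessment described, a patient who leaves at week 7 has a baseline SCCAI and nothing else. An analysis of all randomised patients then has nothing observed under treatment to draw on for that patient.

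The SCCAI items listed under Measurements (stool frequency by day and night, urgency, blood, well-being, external manifestations) need no blood sample or procedure and can be asked of the patient. The trial already reaches each patient at times when they could be asked. Separately, comparing final scores between arms without the baseline score gives up precision that a trial of 44 patients could use.

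What is at stake is the secondary clinical comparison.

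**Working it through.** **Inputs from the article.** 22 patients per arm, 44 in total; 10% loss; scores at baseline and week 12; container returns at the end of each fourth week, hence weeks 4, 8 and 12.

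**Input not in the article.** The correlation r between two SCCAI readings in the same patient. I assume it is equal for every pair of readings and show r = 0.4, 0.6 and 0.8.

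**1. The plan's own sample size.** The 22 per arm rests on TNF-α changes in a cited ginger trial. Effect size and SD are not given, so the figure can be neither confirmed nor refuted. Working backwards at two-sided 0.05 and 90% power, 19 evaluable per arm (19/0.9 = 21.1, rounded up to 22) implies a standardised difference of (1.96 + 1.28) × √(2/19) ≈ 1.05. That concerns TNF-α and says nothing about the clinical scores.

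**2. Patients without a post-baseline score.** 0.10 × 44 = 4.4, so about 4 patients, or roughly 2 per arm.

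**3. Precision gained at week 12 from interim readings.** With complete data, a repeated-measures model with an arm effect at each visit gives the same week-12 contrast as baseline-adjusted analysis of week 12 alone. Any gain comes from patients whose week-12 value is missing. Given baseline, the correlation between two later readings is p = r/(1 + r). Weeks 4 and 8 together then explain a share R² = 2p²/(1 + p) of the remaining week-12 variance. If a fraction f is missing and every leaver has both interim scores (the best case), the variance is multiplied by 1 − f × R², with f = 0.10. For r = 0.4: p = 0.286, R² = 2 × 0.0816/1.286 = 0.13, and the factor is 0.987.

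**4. Precision of the average over weeks 4, 8 and 12.** Relative to one reading, the variance is (1 + 2r)/3. With baseline adjustment on both sides it is ((1 + 2r)/3 − r²)/(1 − r²).

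**5. Baseline adjustment alone.** Relative to unadjusted final values, the week-12 variance is multiplied by 1 − r². This needs no interim reading.

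| Assumed r | R² | Week-12 factor from interim scores | Average, unadjusted | Average, baseline-adjusted | Week-12 factor from baseline adjustment |
|---|---|---|---|---|---|
| 0.4 | 0.13 | 0.987 | 0.60 | 0.52 | 0.84 |
| 0.6 | 0.20 | 0.980 | 0.73 | 0.58 | 0.64 |
| 0.8 | 0.27 | 0.973 | 0.87 | 0.63 | 0.36 |

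**6. Illustration of power.** With 20 evaluable per arm and an assumed clinical effect of 0.5 SD, comparing final values has about 35% power. With r = 0.5, baseline adjustment raises this to about 45%.

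**The case against.** The strongest reply is that measuring a secondary outcome before and after treatment is a legitimate choice in a 44-patient biomarker trial, and that nothing here is contradicted or miscalculated. That is true, and it limits the weight of the point. Because the schedule is stated twice, however, this is a comment on a fixed design choice and not on detail left to a fuller document.

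Three stronger readings are tempting, and the article does not support them.

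- **A large precision gain at week 12.** A reader might apply the ratios 0.60–0.87 to the week-12 comparison. They belong to the average over weeks 4–12, a different estimand. At week 12 the interim scores bring about 1–3%. Any power gain for the average also presumes that the effect is already present at week 4.
- **Worsening patients are the ones lost.** A reader might infer that the final comparison will be among those who did well. This is plausible, but the 10% is a planning allowance with no reasons given. Some patients may leave before week 4 or be unreachable, and interim scores would not help them.
- **The clinical objective rests on one noisy reading.** Two scales are taken at week 12, and percentage-change and adjusted analyses are planned. Calling the disease recurrent describes its long course. No within-patient SD is given.

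Several practical objections stand. The weekly contact may be only an SMS. The article does not say that container return is a clinic visit or who would score the index. Phone and in-person scoring may differ. PMS includes a physician's assessment, so it is not a candidate for phone scoring. The end of the intervention might be read to include a patient's own early stop, but no such assessment is described. The adjusted model could include the baseline score, since its covariate list is open, but it is not named and the primary comparison is of final values.

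**Conclusion.** The point holds as an inexpensive improvement to a secondary outcome. As written, about 4 of 44 patients would contribute no post-baseline SCCAI, and the main between-group comparison ignores the baseline score. This assumes that the 10% allowance is met and that leavers are not scored when they stop.

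The benefit of interim scores is mainly that early leavers' partial data enter the week-12 analysis. This relies on the data being missing at random given the recorded scores, and it reduces missing-data bias without removing it. The precision gain at week 12 from these scores is small, about 1–3% of variance at best. Baseline adjustment yields more, about r² of the variance (16%, 36% and 64% at r = 0.4, 0.6 and 0.8). The lower values are the safer guide, because the readings are 12 weeks apart in patients selected for active disease. All these figures depend on an assumed, equal correlation that the article does not report.

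**What to change.** - **Collect** the SCCAI at weeks 4 and 8 at the existing contacts, in the same mode for both arms, and at last contact in any patient who stops early. State who scores it and how.
- **Analyse** it in all randomised patients with a repeated-measures model containing baseline SCCAI, visit, arm and arm-by-visit. Name week 12 as the time point of interest, and pre-specify the weeks 4–12 average as a supporting estimate. State the missing-at-random assumption.
- **Leave unchanged** PMS, blood sampling, the primary biomarkers and the sample size.

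**Cost.** A few minutes of questionnaire and data entry per contact, and one additional model. If weeks 4 and 8 are scored by phone and week 12 in person, mode differences may blur the time course, though using one mode across arms protects the arm comparison. Assessor time at container return may be needed, since staffing there is not described. Trial status reports that recruitment began in July 2019, so the change needs an amendment and would reach only patients not yet past week 4 or week 8. For those already past, baseline adjustment of the week-12 SCCAI is still available at no data-collection cost.

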### Randomization and blinding

The patients will be randomly allocated to one of the intervention group (Group A) (standard treatment + ginger capsules, *n* = 22) or control group (Group B) (standard treatment + placebo capsules, *n* = 22). Random allocation sequence will be generated using a random number table by a third party who will be operationally independent from the study investigators and will generate a simple design. Ginger and placebo bottles will be also encoded based on random numbers by someone other than researchers, and odd or even numbers will be allocated randomly to Group A or Group B. To decrease the probability of bias, clinicians and those analyzing the results will be blind to the allocated groups. To maintain blinding, ginger and placebo bottles will be similar in appearance. Randomization codes of the study will remain confidential until all the patients have completed the study protocol.

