### Analysis

The data will be analyzed using the Statistical Package for the Social Sciences (IBM SPSS Statistics 22. Ink). Normality of all quantitative variables (age, serum level of TNF-α, hs-CRP, TAC, and expression of mir-21) will be also evaluated by the Kolmogorov-Smirnov test. For normal distribution variables, independent sample t-test and paired sample t-test will be also used to compare parameters at the beginning and the end of the study between and within groups, respectively. The Mann-Whitney U test and Wilcoxon signed-rank test as nonparametric alternatives will be further applied to compare sample parameters between and within groups, respectively. In adjusted models for confounding variables (such as the type of medication), a general linear model (GLM) (univariate type) will be used for each certain parameter to compare mean values between groups. For each certain variable (primary and secondary outcomes), the percentage change will be also calculated (i.e., by subtracting the beginning from the final value, dividing by the beginning value, and multiplying by 100) and will be compared between groups by independent sample t-test or Mann-Whitney U, as well as by GLM univariate tests. The results will be presented as the mean ± SD, and differences will be considered statistically significant at *p* < 0.05. Intention-to-treat analysis will be employed if possible.

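### No between-group analysis is stated to adjust for the outcome's own baseline value, although every outcome is measured at baseline

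*Protocol article*

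**What the plan says.** The protocol article describes four uses of the data in two places.

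- **Hypothesis and aim.** For every primary and secondary outcome, measured at the start and end of the intervention, "changes from baseline within groups and final values between groups will be evaluated".
- **Analysis, unadjusted tests.** Independent and paired t-tests are used "to compare parameters at the beginning and the end of the study between and within groups, respectively". Mann-Whitney and Wilcoxon signed-rank tests are the non-parametric alternatives. The wording includes a between-group test at the start of the study.
- **Analysis, adjusted model.** "In adjusted models for confounding variables (such as the type of medication), a general linear model (GLM) (univariate type) will be used". The covariate list is open; its one example is type of medication, and the outcome's baseline value is not mentioned.
- **Analysis, percentage change.** "For each certain variable (primary and secondary outcomes), the percentage change will be also calculated", and it "will be compared between groups by independent sample t-test or Mann-Whitney U, as well as by GLM univariate tests".

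The Sample size section gives the design figures: "Considering a type I error of 0.05, a test power of 90%, and follow-up loss of 10%, the sample size required in each group" comes to 22. It states the basis as follows: "The sample size was based on the changes observed in the TNF-α". No mean difference or SD is reported.

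**The concern.** TNF-α, hs-CRP, total antioxidant capacity, miR-21 expression and both clinical scores are recorded before treatment. A patient's own starting value is usually among the best predictors of the final value. A final-value comparison without it leaves predictable variation in the error term, and any chance baseline difference between the arms passes in part into the estimated effect. The trial has 22 patients per arm ("standard treatment + placebo capsules, *n* = 22" for the control group), and the Randomization and blinding section describes a simple allocation, so no balancing on baseline is described.

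Percentage change divides by the baseline but does not adjust for it. When r is below 1 it tends to over-correct, so an imbalance is carried with the opposite sign. It also becomes skewed when markers are skewed.

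Two lesser matters belong here. A paired test inside one arm does not compare treatments: patients enter with active disease and continue their prescribed drugs, so both arms may improve. And significance tests of baseline differences tell the reader nothing useful after randomisation.

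**Working it through.** **1. The plan's own figure.** The 22 per group cannot be reproduced, because no difference or SD is given. It can be back-solved. With 10% loss, 22 corresponds to 19 evaluable (19/0.90 = 21.1, rounded up to 22) or 20 evaluable (20 × 1.10 = 22). For two-sided α = 0.05 (sidedness is not stated) and 90% power, the implied standardised difference is d = (1.960 + 1.282) × √(2/n):

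- n = 20: d = 1.025
- n = 19: d = 1.052

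I use n = 20 and d = 1.025 below, and treat the 90% as applying to final values. That is an assumption, since the section speaks of changes in TNF-α.

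**2. Precision.** With equal SDs at both times and correlation r, the variance relative to a final-value comparison is 2(1 − r) for a change score and 1 − r² for the baseline-adjusted model (ANCOVA). Power is Φ(d / √(2v/20) − 1.960), where v is that ratio.

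| Assumed r | Final value: power | Change score: v, power | ANCOVA: v, power | ANCOVA: n per arm for 90% |
|---|---|---|---|---|
| 0.3 | 90.0% | 1.40, 78.2% | 0.91, 92.5% | 19 |
| 0.5 | 90.0% | 1.00, 90.0% | 0.75, 96.3% | 15 |
| 0.7 | 90.0% | 0.60, 98.7% | 0.51, 99.5% | 11 |

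Example at r = 0.5: 3.242/√0.75 = 3.743; 3.743 − 1.960 = 1.783; Φ = 0.963. The gain over final values is about 2.5, 6 and 9.5 percentage points.

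**3. Percentage change.** There is no simple formula, so it was simulated: 20 per arm, log-normal markers, a shift of 1.025 log-SDs, and 3,000 runs per setting. Final value and ANCOVA were analysed on the log scale, percentage change on the raw scale.

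| Log-SD | r | Final value | ANCOVA | % change, t-test | % change, Mann-Whitney |
|---|---|---|---|---|---|
| 0.3 | 0.3 | 88.2% | 91.0% | 75.9% | 75.9% |
| 0.3 | 0.5 | 88.1% | 95.0% | 88.0% | 86.9% |
| 0.3 | 0.7 | 88.2% | 99.0% | 98.0% | 98.0% |
| 0.8 | 0.3 | 88.4% | 90.3% | 60.6% | 74.1% |
| 0.8 | 0.5 | 88.3% | 94.7% | 76.6% | 86.5% |
| 0.8 | 0.7 | 87.3% | 98.9% | 95.2% | 97.6% |

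Percentage change is below ANCOVA in every row, and below the final-value test at r = 0.3. At r = 0.7 it beats the final-value test and comes close to ANCOVA. Part of the t-test's loss at log-SD 0.8 is skewness. The Mann-Whitney column is free of that, because percentage change and log-ratio rank patients identically, and it still falls short of ANCOVA.

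**4. Chance imbalance.** The SE of a baseline difference in SD units is √(2/20) = 0.316. The probability of a difference of at least 0.5 SD in either direction is 2 × [1 − Φ(0.5/0.316)] = 2 × [1 − Φ(1.581)] = 0.114. It is about 5.7% in any one direction. Given a 0.5 SD imbalance, the final-value difference shifts by r × 0.5 = 0.15, 0.25 or 0.35 SD at r = 0.3, 0.5 or 0.7. A change score shifts by (r − 1) × 0.5 = −0.35, −0.25 or −0.15 SD. ANCOVA removes the shift when its linear model holds.

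**5. Within-arm tests.** If both arms truly improve equally and each paired test has power p, ginger is significant and placebo is not with probability p(1 − p). At p = 0.48 (paired t-test, n = 20, assumed change of 0.45 SD) this is 0.48 × 0.52 = 0.25, essentially the maximum of p(1 − p). At p = 0.20 or 0.80 it is 0.16; at p = 0.90 it is 0.09.

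**The case against.** A reader of the aims alone might infer that change from baseline is tested only inside each arm and that the baseline never enters a treatment comparison. The Analysis section contradicts this: percentage change is compared between groups for every primary and secondary outcome, with and without the linear model. That stands, and it limits the point to how the baseline is used.

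The covariate list is also open, the article is condensed, and an analysis plan may name the baseline value. That is fair as regards the full list. But the article goes further than leaving the matter open: it states which between-group contrasts will be made, and the one named in the aims is the unadjusted final value.

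A reader might also infer that the final-value comparison is biased, or that efficacy will be claimed because ginger reaches significance and placebo does not. The documents support neither. Randomisation makes the comparison unbiased on average, the placebo arm deals with regression to the mean, and no section says that within-arm significance will decide efficacy. The 25% figure is close to the worst case and rests on a change of 0.45 SD that no section supplies.

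Finally, the gain depends on an unknown correlation. Restricting entry to moderate or severe partial Mayo scores narrows the baseline range and may lower r, at least for that score. If r is near 0.3, the gain is small.

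**Conclusion.** The point holds in limited form. The plan names unadjusted final values as its between-group contrast and adds a confounder-adjusted model and percentage change. It does not state that any of them adjusts for the baseline value of the outcome. The cost is lost precision (9%, 25% and 49% of the final-value variance at r = 0.3, 0.5 and 0.7) and sensitivity to a baseline imbalance of 0.5 SD or more in about one trial in nine. Bias is not part of the charge.

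These sizes assume 20 evaluable patients per arm, two-sided 0.05, equal SDs at both times, and 90% power for final values. The simulation also assumes log-normal markers. The documents do not give the correlation, the SDs or the distribution. The variance ratios do not depend on the back-solved effect; the power figures do. Because the plan remains valid and the gain is uncertain, this is a recommended improvement and not a condition for proceeding.

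**What to change.** For each outcome, state that the main between-group analysis is the linear model already planned: week-12 value on treatment arm, with the baseline value of that outcome and baseline medication type as covariates. Report the adjusted difference with its 95% CI. Where a marker is skewed, log-transform both time points, so that the difference back-transforms to a ratio, or use a rank-based version.

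Keep the final-value and percentage-change comparisons as supportive analyses. Report within-arm changes descriptively, and say that they are not evidence of a ginger effect. Drop significance tests of baseline differences and show baseline summaries by arm instead.

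The cost is a few sentences. Both measurements are already scheduled and the software is already chosen; the baseline value costs one degree of freedom. The change should be fixed and dated before the randomisation codes are released.
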